### Blinding – single blind

Baseline measures will be taken prior to allocation of randomisation. Independent investigators assessing participants at the end of the programme and at three, six and 12 month follow-up visits or phone calls will be blind to the allocation of the treatment group. Participants will be asked not to discuss group allocation with the assessing professional. Moreover, the person who carries out the analysis of the data will not be involved in the investigation.

### Outcome measures

#### Main objective

The primary outcome measured is adherence, means of increasing physical activity level assessed with short-version IPAQ questionnaire [37]. The study measure will be assessed at baseline, at the end of the intervention, and at three, six and twelve months follow-up.

The level of physical activity will be evaluated, moving from a low level to a moderate or high level, or increasing the weekly number of Metabolic Equivilent Units (MET). The IPAQ enables physical activity to be evaluated as a continuous variable by calculating the weekly METs, and classifying the subjects according to whether they have a low, moderate or high level of physical activity. This instrument has shown good validity and reliability in general population in a previous study [37].

#### Other specific objectives

Secondary outcomes for IG and CG include: (a) decreasing the number of visits to the healthcare centre by individuals involved in the programme, registering the total number of visits during the six months before and after the programme; (b) description of the development of quality of life related to health, measured with SF-12 test [39,40] (the first and last session of the programme) and evaluation of short, medium and long term evolutions, with follow up at three, six and twelve months after the programme has finished; c) description of the evolution of perceived health status, measured with the COOP/WONCA vignettes (first and last session of the programme) [41]. This instrument showed good validity and reliability in general population in a previous study [41]; (d) evaluation of the attitude towards the change in behaviours in relation to regular exercise using the Prochaska scale (first session and six and twelve months after finalising the project) [42]; (e) evaluation of the social support for the physical activity practice, assessed using the SSPAS scale [43] (first and last session of the programme and three, six and twelve months after finalising the intervention). Reliability and validity of the scale was previously assessed in an elderly population [43]; and (f) description of the evolution of HDL, LDL and glycosilate hemoglobin (first and last session and 6 and 12 months after finalising the programme). Demographic and health data will be also collected (age, blood pressure, heart beat when resting, weight, height, body mass index, current medication and associated pathologies).

### Data management and quality assurance

Data will be entered directly into a customized Microsoft Access database by investigators at the time of the interview and baseline testing. Daily backups will be performed and transferred to the master database at least once a week. Random checks of data entry will be performed regularly and corrections made will be possible by checking against paper records or, in rare cases, by phoning participants for confirmation by independent investigators.

### Sample size

Accepting an alpha risk of 0.05 and a beta risk of 0.20 in a bilateral contrast, 424 individuals are needed: 212 individuals in the IG and 212 in the CG in order to detect a difference equal to or higher than 0.15 between the two [23]. A proportion of 0.5 in one of the groups is to be assumed. A dropout rate of 16% is estimated, based on the pilot study experience [34].

### Statistical methods

Analysis of effectiveness will be made followed by the intention to treat analysis. The analysis of data will be made using the SPSS statistic software version 15.0 and STATA, version 9.1. In all cases a bilateral alfa error of 0.05 will be used and the confidence intervals will be calculated at 95%. Descriptive statistics will be calculated and intervention and control groups will be checked for health and outcome measures at baseline.

A baseline comparability analysis of the CG and IG in relation to the variables studied, will be carried out. An s-Student test or ANOVA will be used in the comparison of means if the variables follow a normal distribution and the U of Mann Whitney if they do not. For the other dimensions of the analysis, a covariance analysis (ANCOVA) for repeated measures will be carried out.

For the multi-variance analysis the change in the time of the described dependent variables will be evaluated, and comparisons between the CG and IG will be established. To do this multilevel linear models will be adjusted, one for each dependent variable. In the first level the individual path or the evolution of each individual over a long period of time (pre-post intervention, 3,6,12 month follow-up) will be modelled. In the second level it will be adjusted according to the variables that refer to the individual; the intervention variable will be added (intervention or control) to the independent variables described earlier.

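### Intention to treat is promised, but repeated-measures ANCOVA in its standard form drops incomplete participants, and the multilevel model beside it has no explicit arm-by-visit contrast and no stated priority

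*Protocol article*

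**What the plan says.** Three statements in the Statistical methods section of the protocol article bear on the repeated outcomes.

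- **Population.** "Analysis of effectiveness will be made followed by the intention to treat analysis". The section on the physical activity promotion programme also appears to say, in awkward English, that everyone who consents enters the analysis.
- **First longitudinal method.** After the two-group tests of means, and for what it calls the other dimensions, "a covariance analysis (ANCOVA) for repeated measures will be carried out". The outcomes, visits and covariates are not listed.
- **Second longitudinal method.** "multilevel linear models will be adjusted, one for each dependent variable". Its purpose is that "the change in the time of the described dependent variables will be evaluated, and comparisons between the CG and IG will be established". Level 1 is each person's course over time, "pre-post intervention, 3,6,12 month follow-up) will be modelled", so the pre-intervention value is one of the responses. At level 2, "the intervention variable will be added (intervention or control) to the independent variables described earlier".

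No sentence says which of the two methods decides, and no arm-by-visit term is written out. The Main objective section has the primary outcome measured "at baseline, at the end of the intervention, and at three, six and twelve months follow-up", which is five occasions. The Sample size section gives 212 per arm, a difference of 0.15 from a proportion of 0.5, two-sided alpha 0.05, beta 0.20, and 16% dropout.

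**The concern.** A standard repeated-measures ANCOVA needs a complete set of responses from each person. Anyone with a gap is removed, so the result describes completers, whatever population the plan names. In a trial about adherence, those who stop attending may well be those who stay inactive, and a completer analysis could then favour the intervention.

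The multilevel model does not have that weakness, but its wording leaves the treatment contrast open. If arm only shifts the overall level, the estimate averages in the baseline visit, where randomisation makes the expected difference zero. If arm acts on a straight line in time, the model cannot follow a gain at the end of a supervised three-month programme that later fades. The two methods use different people and possibly different contrasts. They can disagree, and the plan gives no rule for that case.

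**Working it through.** **1. The plan's own figure.** Inputs from the Sample size section: proportions 0.50 and 0.65, two-sided 0.05, power 0.80.

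- Without continuity correction: n = [1.96·√(2·0.575·0.425) + 0.8416·√(0.25 + 0.2275)]² / 0.15² = (1.370 + 0.582)² / 0.0225 = 169.3, so 170 per arm.
- With continuity correction: (169.3/4)·[1 + √(1 + 4/(169.3·0.15))]² = 182.4, so 183 per arm.
- Adding 16%: 183 × 1.16 = 212.3, which rounds to the stated 212 per arm and 424 in total. Dividing instead gives 183/0.84 = 217.9, so 218 per arm.

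The stated figure reproduces. The protocol does not say by which visit the 16% is reached.

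**2. Completers left under the ANCOVA.** 212 × 0.84 = 178.1 per arm. This is an upper limit, because anyone who stays in the trial but misses a visit is lost as well. Power for 0.50 against 0.65 is Φ{[0.15 − 1.96·√(0.48875/n)] / √(0.4775/n)}. Only the 16% is documented; the larger losses are assumed, to show the range.

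| Incomplete | n per arm | Power |
|---|---|---|
| 0% | 212 | 0.88 |
| 16% | 178 | 0.82 |
| 20% (assumed) | 170 | 0.80 |
| 25% (assumed) | 159 | 0.775 |
| 30% (assumed) | 148 | 0.746 |
| 40% (assumed) | 127 | 0.679 |

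Two cautions apply. These powers carry no continuity correction; on the corrected formula that best reproduces 424, 183 per arm are needed and 178 is already five short. They also refer to a comparison of proportions, whereas the ANCOVA compares means, so they indicate the scale of the loss and are not the power of the ANCOVA.

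**3. Bias if dropout relates to activity (assumed rates).** Take no true effect, half of each arm responding, control-arm dropout unrelated to response, and 16% average dropout in the intervention arm.

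- Both groups drop out at 16%: no bias.
- Non-responders 20%, responders 12%: 0.5·0.88/0.84 = 0.524, a false gain of 2.4 points.
- Non-responders 24%, responders 8%: 0.5·0.92/0.84 = 0.548, a false gain of 4.8 points.

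The protocol gives no such split. The lines show only how the bias grows with the imbalance.

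**4. Multilevel model, if arm enters only as a main effect.** With a random intercept, complete data and m waves, the arm coefficient is the plain mean of the m visit-specific differences. For a constant effect d after baseline:

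- five waves: (0 + d + d + d + d)/5 = 0.80d;
- in general (m − 1)/m, so 0.75d with four waves, 0.67d with three and 0.50d with two.

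**5. Multilevel model, if arm acts on a straight line in time.** The visits fall at months 0, 3, 6, 9 and 15 from baseline, since follow-up is counted from the end of a three-month programme. Suppose the arm differences are 0, d, 0.75d, 0.5d and 0.25d (an assumed rise then decline). Mean time is 6.6 and mean difference 0.5d. The centred cross-product is −0.75d and the centred sum of squares 133.2.

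- Slope: −0.75d/133.2 = −0.00563d per month, or −0.084d over 15 months.
- Intercept: 0.5d + 0.00563d × 6.6 = 0.54d.
- Fitted differences: 0.54d at baseline (0 in the data), 0.52d at month 3 (d in the data), 0.45d at month 15 (0.25d in the data).

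The line puts a difference where randomisation expects none, halves the early gain and overstates the late one.

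**The case against.** The strongest reply is that the text is ambiguous rather than wrong. Much of it stands.

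- **Only completers are analysed?** A reader might infer that the plan as a whole keeps only people with every visit, in open contradiction of intention to treat. The documents do not support that. Deletion of incomplete cases is how the usual procedure works, not something the protocol states, and the multilevel model, promised for every dependent variable, can use all available visits. The handling of missing visits may also sit in a fuller document. What remains is that the named ANCOVA, run in its standard form, does not fit the named population.
- **The multilevel model dilutes or hides the effect?** A reader might infer this from the level-2 wording. However, the stated purpose is to compare change over time between arms, and a level-2 variable can act on slope as well as on level. Neither a main effect alone nor a straight line in time is written. Steps 4 and 5 are therefore conditional. Nor would the linear-time model report nothing: the near-zero slope in step 5 comes with an arm intercept of 0.54d.
- **Five visits throughout?** No. The section on other specific objectives measures the COOP/WONCA vignettes twice, the Prochaska scale three times and the laboratory values four times. The scope of the ANCOVA is unclear, and it may not be meant for the primary outcome.
- **A mixed model does not cure all dropout bias.** If dropout depends on unobserved activity, it shares the problem in step 3. That is a reason for a sensitivity analysis, not for keeping the ANCOVA.

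The reply does not remove the difficulty that the article chose to name two methods, with their levels and response occasions, without ranking them or writing out the contrast.

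**Conclusion.** The point holds in a limited form. The repeated-measures ANCOVA, followed in its standard form, yields a completer analysis beside a promise of intention to treat. On the documented 16% it keeps at most about 178 of 212 per arm. The loss of power is then modest (0.88 to 0.82) and becomes a shortfall only beyond about 20% incomplete. Possible bias is the more serious consequence, but its size rests on assumed dropout patterns.

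For the multilevel model the finding is lack of precision, not demonstrated error. The figure 0.80d holds only for a main-effect fit with five complete waves and a constant effect. The poor fit to a rise then decline holds only for a linear-time interaction. Visit-specific arm contrasts would avoid both, and the text does not state them. The absence of any order between the two methods is a defect in its own right. The change is worth making before the data are analysed.

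**What to change.** Remove the repeated-measures ANCOVA and make the multilevel model the single stated longitudinal analysis:

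- fit it by likelihood to all randomised participants, using every available visit;
- treat visit as categorical, with arm-by-visit terms;
- use baseline as a covariate, or keep it as a response constrained equal between arms;
- report the arm difference with its 95% confidence interval at each follow-up visit that the outcome has;
- have the sponsor name which visit is decisive for the primary outcome, since the protocol leaves this open;
- add a sensitivity analysis in which participants who drop out are assumed to do worse than the model predicts, over a stated range.

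The cost is a few sentences and a little more analysis work. The plan already relies on "SPSS statistic software version 15.0 and STATA, version 9.1" for multilevel models. No new data, visits or participants are needed.

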**Method and design:**

Randomized controlled trial with systematic random sampling. A total of 424 subjects of both sexes will participate; all will be over the age of 18 with a low level of physical activity (according to the *International Physical Activity Questionnaire*, IPAQ), self-employed and from 9 Primary Healthcare Centres (PHC). They will volunteer to participate in a physical activity programme during 3 months (24 sessions; 2 sessions a week, 60 minutes per session).

Participants from each PHC will be randomly allocated to an intervention (IG) and control group (CG). The following parameters will be assessed pre and post intervention in both groups: (1) health-related quality of life (SF-12), (2) physical activity stage of change (Prochaska's stages of change), (3) level of physical activity (IPAQ-short version), (4) change in perception of health (vignettes from the *Cooperative World Organization of National Colleges, Academies, and Academic Associations of Family Physicians*, COOP/WONCA), (5) level of social support for the physical activity practice (*Social Support for Physical Activity Scale*, SSPAS), and (6) control based on analysis (HDL, LDL and glycated haemoglobin).

Participants' frequency of visits to the PHC will be registered over the six months before and after the programme. There will be a follow up in a face to face interview three, six and twelve months after the programme, with the reduced version of IPAQ, SF-12, SSPAS, and Prochaska's stages.

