### Intervention

#### Physical activity promotion programme

When a patient agrees to participate an assigned professional health worker will send a registration form to the investigation team and to the specialist who will lead the exercise group. The patient will be contacted by telephone to carry out the evaluation and to start the intervention. All participants will report to the healthcare centre twice a week for 12 weeks, and all participants who hand in a consent form will undergo an analysis stating their intention to undergo the treatment.

Each session will last 60 minutes, and all protocols have been developed for progressive intensity. The sessions will be carried out by physical activity specialists in a room in the health centre itself, in nearby exterior locations (parks, squares, etc) or in municipal facilities in the same district. Table 1 shows the contents of the programme [35]. At the same time, participants will be shown exercises that they should do at home. It is recommended that from the first day, a minimum of three sessions per week be done at home without supervision and without keeping a record.

**Table 1 T1:** Components of the exercise programme [35]

**Component**	**Includes these exercises**	**Repetitions per exercise**^a^	**Duration of a single exercise or repetition**	**Duration per 60 minutes class**	**Major benefits**
**Warm-up**	- Range-of-motion. - Low-intensity aerobics.	4–8	2 seconds per repetition	10 minutes minimum	- Increases internal body temperature. - Injury prevention.

**Aerobics**	- Aerobic exercises (e.g. walking, swimming, cycling)	Varies	Varies	15–30 minutes	- Cardio respiratory endurance.

**Resistance training**	- Body- weight^b ^exercises. - Resistance exercises.	8–15	6 seconds per repetition	15–30 minutes	- Muscular strength and endurance.

**Cool-down**	- Stretching.	1	30–45 seconds per stretch	5–30 minutes	- Improved flexibility.

	- Relaxation techniques. - Stress-reduction techniques.	Varies	Varies	5–30 minutes	- Relaxation, stress reduction.

^a^Several factors determine the number of repetitions, such as the component of exercise, the level of fitness of the participant, the level of progress for that exercise, day-to-day variations in the participant's state, and the total amount of time available for the exercise class.

^b^Body-weight exercises are exercises in which one's body weight, such as the weight of one's arm or legs, serves as the resistance.

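### The intervention arm is treated in led exercise groups, but the two-level model has no exercise-group term and the sample size assumes independent individuals, so the treatment-effect standard error is too small if outcomes correlate within groups

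*Protocol article*

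**What the plan says.** Allocation is of individuals, within centre. The Abstract states: "Participants from each PHC will be randomly allocated to an intervention (IG) and control group (CG". Recruitment process gives nine centres and a target of 50 subjects in each.

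Delivery differs between the arms. Under Physical activity promotion programme, registration forms go to "the specialist who will lead the exercise group", and sessions run twice a week for 12 weeks. The Discussion presents training alongside people from the same neighbourhood as a feature of the design. Under Control group, controls continue with usual care and are not grouped.

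The Sample size section reads "Accepting an alpha risk of 0.05 and a beta risk of 0.20 in a bilateral contrast, 424 individuals are needed", with 212 per arm, "in order to detect a difference equal to or higher than 0.15 between the two". It adds "A proportion of 0.5 in one of the groups is to be assumed" and a 16% dropout rate. It mentions no ICC, design effect, centre or group.

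Statistical methods sets out the multilevel linear models. The first level is each individual's course over the visits. For the second, "In the second level it will be adjusted according to the variables that refer to the individual", together with the intervention indicator. Neither there nor in the repeated-measures ANCOVA is exercise group or centre named. The test level is fixed: "In all cases a bilateral alfa error of 0.05 will be used".

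**The concern.** This is a partially nested design. IG participants share a leader, a timetable and each other's company; controls share nothing comparable. The article regards the sharing as part of how the programme works: the Background lists lack of social support as a barrier to participation, and social support for physical activity is a measured outcome. Zero correlation within groups therefore sits badly with the trial's own rationale.

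If IG outcomes do correlate within group, the IG mean carries between-group variance that the described model cannot see. The standard error of the treatment effect is then too small, confidence intervals are too narrow and false positives exceed 5%. The error favours a positive result and carries into each outcome model. Power worked out for independent individuals is also optimistic.

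**Working it through.** **Inputs from the article.** Two-sided alpha 0.05, power 0.80, proportions 0.50 and 0.65 (mean 0.575), 212 per arm, 16% dropout, nine centres.

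**Assumptions, because the article gives no figure.** ICC of 0.01, 0.02 or 0.05 among IG completers, and one or two exercise groups per centre (9 or 18 groups).

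**1. Reproducing 424.** The two-proportion formula is n = [1.96·√(2·0.575·0.425) + 0.842·√(0.5·0.5 + 0.65·0.35)]² / 0.15² = 169.3, so 170 per arm. Dividing by 0.84 gives 203. With continuity correction, n = 182.4, so 183 per arm. Dividing by 0.84 gives 218 (total 436). Multiplying the unrounded 182.4 by 1.16 gives 211.6, so 212 per arm and 424 in total. Every variant has design effect 1, so the stated figure holds no allowance for clustering.

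**2. Completers.** 212 × 0.84 = 178 per arm. Average group size m is 178/9 = 19.8 or 178/18 = 9.9.

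**3. Design effect, IG only.** DE = 1 + (m − 1)·ICC.

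**4. Type I error when group is ignored.** With equal variances under the null, the true standard error exceeds the model's by √((1 + DE)/2), and the error rate is 2·[1 − Φ(1.96/ratio)]. For nine groups and ICC 0.02, DE = 1 + 18.8 × 0.02 = 1.376, the ratio is 1.090 and the error rate is 7.2%.

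**5. Power when group is allowed for.** Power = Φ[(0.15 − 1.96·SE0)/SE1], where SE0 = √[0.575·0.425·(1 + DE)/178] and SE1 = √[(0.25 + 0.2275·DE)/178]. For the same case, SE0 = 0.0571, SE1 = 0.0562 and power is 75.1%.

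| Groups | ICC | DE | SE ratio | Type I error | Power |
|---|---|---|---|---|---|
| any | 0 | 1.00 | 1.00 | 5.0% | 81.9% |
| 9 | 0.01 | 1.19 | 1.05 | 6.1% | 78.5% |
| 9 | 0.02 | 1.38 | 1.09 | 7.2% | 75.1% |
| 9 | 0.05 | 1.94 | 1.21 | 10.6% | 65.9% |
| 18 | 0.01 | 1.09 | 1.02 | 5.5% | 80.3% |
| 18 | 0.02 | 1.18 | 1.04 | 6.0% | 78.6% |
| 18 | 0.05 | 1.44 | 1.11 | 7.6% | 73.9% |

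Simulating nine groups of 20 and analysing with a t-test that ignores group gave 7.1% at ICC 0.02 and 10.9% at 0.05. The power column uses normal critical values; with few groups, small-sample degrees of freedom lower it slightly further.

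**6. Recruiting 450.** Nine centres × 50 = 450, or 225 per arm; × 0.84 = 189 completers. At ICC 0.01, 0.02 and 0.05, power becomes 80.6%, 77.2% and 67.6% (nine groups) or 82.5%, 80.8% and 75.9% (eighteen). The type I error does not improve, because larger groups raise DE.

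**7. Centre.** A centre effect common to both arms cancels from a within-centre contrast. Simulating an analysis that ignores it gave type I error between about 4% and 5% at centre ICC 0.05 and 0.10, with no loss of the stated power.

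**The case against.** The strongest objection is that the harm depends on quantities the article does not give. It states no ICC, no group count and no group size. It speaks of specialists in the plural and of several venues, and never says that each centre runs one fixed group. With eighteen groups and a low ICC, type I error is 5.5% to 6.0% and power stays within two points of 80%. Recruiting 450 would cover the lower ICCs. This stands. A reader might infer that the stated power is certainly not delivered, or that beta of 0.20 requires zero correlation; the eighteen-group case at ICC 0.01 keeps 80.3%, so the documents do not support either claim.

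A reader might also infer that leaving out centre does the same damage as leaving out group. It does not. Individuals are allocated within centre, so omitting centre makes standard errors slightly too large, and a cluster-trial design effect on both arms would be wrong.

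The error rates above are for a comparison at one time point, not for the repeated-visit linear model. The direction carries over to that model, but the exact size has not been shown.

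Finally, a journal article may leave model detail to a fuller plan. Here, though, the article sets out both levels and their contents, and these do not match the delivery it describes. That answers the charge that this is mere omission.

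**Conclusion.** The point holds for exercise group in the IG. The stated model makes the treatment-effect standard error too small at any positive intra-group correlation: by about 5%, 9% and 21% in SE ratio with nine groups, or 2%, 4% and 11% with eighteen, at the assumed ICCs of 0.01, 0.02 and 0.05. A nominal 5% test then runs at about 6% to 10.6%, or 5.5% to 7.6%. Power is conditional: with 178 completers per arm it is below 80% from ICC 0.01 with nine groups and from 0.02 with eighteen, though by less than two points at those first values. Enrolling 450 offsets the power loss at the lower ICCs but leaves the type I error uncorrected. Omitting centre neither inflates error nor costs stated power. All the sizes rest on assumed ICCs and group counts. Severity: should-fix.

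**What to change.** 1. Record an exercise-group identifier for every IG participant before sessions start. Recruitment process mentions attendance but not group membership.
2. In every outcome model, add a random effect for exercise group in the IG only, or a random treatment effect by centre if each centre runs one group. Use small-sample degrees of freedom.
3. Include health centre as a factor, for precision.
4. State the expected number and size of groups, and restate power over a range of ICC and group size, as in the table.

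This costs one extra variable and a change of wording. Correcting the type I error needs no extra patients. Intervals will be somewhat wider, and the stated power may fall below 80%. Holding 80% throughout would be a separate decision. Without continuity correction, with 16% dropout and the number of groups held fixed, it would take 222, 246 or 367 per arm with nine groups, or 211, 221 or 256 with eighteen, at ICC 0.01, 0.02 and 0.05; the same formula gives 203 at ICC 0.
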